#### Statistical analysis

The effect of the two training interventions on the outcome measures will be determined using repeated-measures analysis of variance (ANOVA) with two factors: 1) group (perturbation-based training versus control group), and 2) session (pre- versus post-training). Any of the cohort descriptors (measured at baseline, as detailed earlier) that show significant inter-group differences in preliminary univariate analyses will be included as covariates in the main analysis. As noted earlier, the control training program was specifically designed not to improve balance control; therefore, changes in the control group (pre- versus post-training) are expected to represent typical learning effects resulting from repeated exposure to the balance-assessment procedure, as well as possible 'placebo' effects associated with the interventions. Analysis of the group-by-session interaction will therefore reveal any real benefits resulting from the perturbation-based training intervention.

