#### Intervention

Each training program will last six weeks, with three 30-minute sessions per week. This duration and intensity is similar to that used in previous perturbation-based training studies [34,35,39]. All subjects will be asked to refrain from initiating any other new exercise programs, or otherwise consciously changing their activity levels, during their participation in the study. For the perturbation-based training program, each session will consist of 2–3 minutes of preparation and instruction, 10–12 minutes of step training, 3–5 minutes of rest, and 10–12 minutes of grasping training. We aim to complete at least 24 trials of stepping and 24 trials of grasping per session (three sets of eight trials for each).

The control subjects will undergo a flexibility and relaxation program, and will receive the same degree of interaction with experimenters as those in the perturbation-training group. The first session of each week will involve 30 minutes of passive muscular relaxation exercises [70]. The second and third sessions will focus on lower- and upper-body flexibility exercises, respectively. In the flexibility sessions, a ten-minute warm-up (heart rate kept below 60% of maximum) will precede 15 minutes of stretching exercises, (two sets of 7–9 stretches for each muscle group, with each stretch held for 15 seconds). The control program is designed to involve a limited intensity of physical activity, so as to avoid bringing about any significant physiological changes. A similar, but more intense, flexibility and relaxation program failed to reduce falling [9], or brought about only moderate improvements in falls risk [71]. Subjects will be asked not to practice the relaxation or flexibility exercises outside of the scheduled sessions during the study.

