Other secondary outcome measures will be analysed to evaluate whether the training had any benefits extending beyond effects on balance reactions. We will explore indirectly the effect on overall falls risk using the FallScreen^© ^battery noted earlier. In addition, we will explore effects on: 1) balance confidence (Activity-specific Balance Confidence questionnaire [62]); 2) mobility ('Timed Up & Go' test [77]); 3) flexibility (modified 'sit and reach' test [78]); and 4) lower-limb power (using the repeated step-up test [79] as a proxy measure [80]).

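### The rule that the group-by-session interaction shows the real benefits of perturbation training does not carry over to sit-and-reach, because the control arm is trained in flexibility

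*Protocol article*

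**What the plan says.** Under Statistical analysis, one model serves all outcomes: "The effect of the two training interventions on the outcome measures will be determined using repeated-measures analysis of variance (ANOVA) with two factors", group and session. The section then explains how to read it. Because "the control training program was specifically designed not to improve balance control", pre-to-post changes in controls "are expected to represent typical learning effects resulting from repeated exposure to the balance-assessment procedure", together with possible placebo effects. From this it concludes: "Analysis of the group-by-session interaction will therefore reveal any real benefits resulting from the perturbation-based training intervention".

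Under Outcome measures, after the balance-reaction measures: "Other secondary outcome measures will be analysed to evaluate whether the training had any benefits extending beyond effects on balance reactions". The measures named are the FallScreen falls-risk battery, balance confidence, Timed Up & Go, flexibility by a modified sit-and-reach test, and lower-limb power. They are described as exploratory. Table 2 marks flexibility as measured before and after the intervention.

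Under Intervention, the control arm has three 30-minute sessions a week for six weeks. The first session of each week is relaxation. For the others: "The second and third sessions will focus on lower- and upper-body flexibility exercises, respectively". Each flexibility session includes 15 minutes of stretching. The same section says the control program was kept at limited intensity to avoid significant physiological change. It adds that a similar but more intense program either failed to reduce falling or "brought about only moderate improvements in falls risk".

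**The concern.** The argument under Statistical analysis has a narrow premise and a wide conclusion. The premise concerns balance control and repetition of the balance tests. The conclusion speaks of any real benefit, in a section that covers the outcome measures without restriction. For stepping and grasping outcomes the two fit together. For sit-and-reach they do not, because the comparator is a flexibility program and the outcome is flexibility.

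What is at stake is how one exploratory result is read. Read by the stated rule, a null interaction would be reported as no flexibility benefit of perturbation training and a negative one as harm. A real stretching gain in controls would be reported as a test-repetition or placebo effect.

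**Working it through.** **Contact with flexibility training, from Intervention**

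- Control arm: 2 flexibility sessions per week × 6 weeks = 12 sessions, 6 lower-body and 6 upper-body. At 15 minutes of stretching each, that is 12 × 15 = 180 minutes, of which 6 × 15 = 90 are lower-body.
- Perturbation arm: each session consists of preparation and instruction, step training, rest, and grasping training. No stretching is listed. Table 1 includes reaching and trunk-twist tasks, but only as concurrent tasks while waiting for a perturbation.

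**Does the stated explanation of control change reach sit-and-reach?** It names repeated exposure to the balance-assessment procedure. The balance tests are set out in Table 3, and sit-and-reach is not among them; it is a separate measure in Table 2. The design premise (no improvement in balance control) says nothing about flexibility.

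**What the interaction estimates.** Let *p* be the true effect of perturbation training on the outcome, *s* the true effect of the control program, and *r* the repetition and placebo effect, taken as equal in both arms. Then

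interaction = (*p* + *r*) − (*s* + *r*) = *p* − *s*.

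The control arm removes *r*, as the plan intends. The result equals *p* only if *s* = 0. For sit-and-reach nothing in the document supports *s* = 0 beyond the stated intention to keep intensity low.

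**Size.** The plan gives no figure for this outcome, so there is none to reproduce. The values below are assumptions, in units of the SD of change, with the planned 15 per group from Sample size estimate and a two-sided t-test at 0.05 (the plan gives 0.05 without stating sides).

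| *p* | *s* | Interaction | Chance of a significant result |
|---|---|---|---|
| 0.5 | 0 | 0.5 | 26% |
| 0.5 | 0.25 | 0.25 | 10% |
| 0.5 | 0.5 | 0 | 5% |
| 0.5 | 0.8 | −0.3 | 13% |
| 1.0 | 0 | 1.0 | 75% |
| 1.0 | 0.5 | 0.5 | 26% |
| 0 | 0.5 | −0.5 | 26% |
| 0 | 0.8 | −0.8 | 56% |

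Equal gains cancel. A true gain of 1.0 SD falls from a 75% to a 26% chance of detection if controls gain 0.5 SD. With no effect of perturbation training at all, a control gain of 0.5 or 0.8 SD gives about a 26% or 56% chance of a significant difference against it.

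**The case against.** The best defence is that the reasoning under Statistical analysis is about balance throughout, and that the section opens by describing the effect of two interventions, which is a between-program comparison. It never says that a sit-and-reach gain in controls would be called learning. The control program was deliberately kept light, the outcome is exploratory, and few readers would mistake a result favouring a program openly named flexibility and relaxation for harm from platform training.

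Part of this stands. The consequence is small, and misreading as harm is less likely than misreading as no benefit. But the conclusion is worded for any benefit, the model is applied to all outcome measures, and sit-and-reach is expressly listed as a possible benefit. Limited intensity is a design intention; it does not show that 12 flexibility sessions leave flexibility unchanged.

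Three stronger readings are tempting, and the documents do not support them:

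- *That the interaction does not measure benefit at all.* It remains a valid randomised contrast between two programs. A control gain pulls it against perturbation training, so a positive value would still show an advantage over the control program. Only null and negative values are ambiguous.
- *That FallScreen is compromised in the same way.* The earlier program that gave moderate improvement in falls risk was more intense than this one, and the same sentence also reports a failure to reduce falling. Table 2 does not mark sit-and-reach as a FallScreen item. A control effect is possible, not established.
- *That state anxiety is biased because controls receive relaxation.* Table 2 shows it is re-measured, but as a cohort descriptor. Outcome measures does not list it, and nowhere is a group difference in it to be read as a benefit.

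**Conclusion.** The point holds for sit-and-reach, as a fault of interpretation and not of the model. The stated inference does not follow for that outcome, because its premise covers balance control and the control arm is trained directly in flexibility. The direction of any bias is against perturbation training and its amount equals the control program's own effect on flexibility, which the documents do not give. This assumes that repetition and placebo effects are similar in the two arms. For FallScreen only a caution in labelling is warranted. The four primary outcomes, the main hypothesis about stepping and grasping, and the sample size are untouched, so this is a minor point.

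**What to change.** 1. Under Statistical analysis, limit the sentence on real benefits to the balance-reaction outcomes, for which the reason given applies.
2. Under Outcome measures, take sit-and-reach out of the list of possible training benefits. Report it as a check on the control program, described as a comparison with active flexibility training, and state that a null or negative difference is not evidence of no benefit or of harm.
3. Describe the FallScreen result as a comparison with a flexibility and relaxation program, noting that a control effect is possible. Within-arm changes would not replace the between-arm difference, since they bring back the repetition and placebo effects that the control arm is there to remove.

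The cost is wording only: no change to data collection, model, randomisation or sample size.

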#### Sample size estimate

To date, five subjects have completed the perturbation-based training and five have completed the control intervention. Sample size calculations for repeated measures ANOVA [81] were performed using the variance from these initial ten subjects. Separate calculations were performed using two of the primary outcome measures, so as to determine the sample-size requirements based on stepping reactions (average number of 'extra' steps taken to recover balance) and grasping reactions (handrail-contact time). For both calculations, probability of Type I error was 0.05, and probability of a Type II error was 0.2.

A previous study of older adults showed that the average number of 'extra' steps taken to recover balance was 1.21 in 'fallers' and 0.825 in 'non-fallers' [25]. This suggests that a reduction equal to 0.5 steps, due to the perturbation-based training, will have functional significance. Using this value, in combination with the initial variance estimate (SD = 0.44 steps), it was determined that 15 subjects per group will be required. For grasping responses, the previous study [25] indicated that handrail-contact time was delayed by 50 ms, on average, in the 'fallers'. Detection of a training effect of this size, given the initial variance estimate (SD = 39 ms), requires a sample of only 12 subjects per group. Thus, to ensure sufficient statistical power for both stepping and grasping measures, it appears that 15 subjects per group will be required. However, sample-size requirements will be re-evaluated at two intermediate stages, i.e. after completing 10 and 15 subjects in each group. If any subjects are still enrolled in either training program when the new estimate for the required number of subjects is reached, these remaining subjects will complete the study and the tested sample will exceed the estimated requirement.

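### The sample-size re-evaluation at 10 per group can end recruitment below the planned 15; no minimum is set and the final test takes no account of it (minor, cheap to repair)

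*Protocol article*

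**What the plan says.** The section Sample size estimate takes its variances from the first ten completers, five per group. It states: "For both calculations, probability of Type I error was 0.05, and probability of a Type II error was 0.2".

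- **Stepping:** it argues that "a reduction equal to 0.5 steps, due to the perturbation-based training, will have functional significance", and from the "initial variance estimate (SD = 0.44 steps), it was determined that 15 subjects per group will be required".
- **Grasping:** the target is 50 ms, which, "given the initial variance estimate (SD = 39 ms), requires a sample of only 12 subjects per group".

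The larger figure, 15, is adopted, in line with the total of 30 in the Abstract. The section then adds that "sample-size requirements will be re-evaluated at two intermediate stages, i.e. after completing 10 and 15 subjects in each group". The sentence that follows begins "If any subjects are still enrolled in either training program when the new estimate for the required number of subjects is reached" and provides that such subjects will finish, so that the sample overshoots the estimate. This implies that recruitment stops when the new estimate is reached, whether that lies above or below 15. No minimum is given, and nothing says whether the SD is computed within groups or on all subjects pooled as one sample.

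The section Statistical analysis specifies a repeated-measures ANOVA with the group-by-session interaction as the test of benefit. It does not mention the re-evaluation. The section Randomisation and blinding says that only the trainer knows the allocation.

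**The concern.** An SD from 10 per group is imprecise. If it comes out low by chance, the new requirement falls below 15 and recruitment ends. If that SD was computed within groups, the same low value largely determines the error term of the final test, so the test statistic tends to be too large in just those trials. Any excess of false positives is therefore concentrated in the trials that stop early.

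The other stake is information. A fixed 10 per group has power 0.67 at SD 0.44, against 0.85 for a fixed 15. Only two of the four primary outcomes enter the calculation. A cut based on those two also reduces the data on foot collisions and additional lateral steps, for which no sample-size calculation is reported.

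**Working it through.** **Inputs from Sample size estimate:** alpha 0.05, power 0.80, effects 0.5 steps and 50 ms, SDs 0.44 steps and 39 ms, looks at 10 and 15 per group.

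**Assumptions:** two-sided test; SDs are those of the pre-to-post change; normal data; no dropout; a cap of 60 per group in the simulation. With two sessions, the interaction test equals a t test on change scores.

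**1. The plan's own figures.** n = 2(1.960 + 0.842)² × SD²/effect².
- Stepping: 62.79 × 0.44² = 12.2, so 13. Exact t gives 14. Stated: 15.
- Grasping: 2(2.802 × 39/50)² = 9.55, so 10. Exact t gives 11. Stated: 12.

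Both stated figures are reproduced to within 2. Two re-evaluation rules are carried forward: the normal formula (A), and a rule scaled to return the document's 15 at SD 0.44, n = 15 × SD²/0.44² (B).

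**2. Interim SD that gives fewer than 15 per group.**
- Rule A: SD² ≤ 14/62.79, so SD ≤ 0.47. It gives 10 or fewer if SD ≤ 0.40.
- Rule B: SD² ≤ 0.44² × 14/15, so SD ≤ 0.43. It gives 10 or fewer if SD ≤ 0.36.

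**3. How often this happens if the true SD is 0.44.** The within-group SD at 10 per group has 2 × 10 − 2 = 18 df, so 95% of estimates fall between 0.30 and 0.58.
- Stepping alone: P(χ²₁₈ ≤ 20.7) = 0.71 under A; P(χ²₁₈ ≤ 16.8) = 0.46 under B.
- Larger requirement rules, outcomes assumed independent, grasping SD 39 ms: grasping alone falls below 15 with probability 0.91 (A) or 0.72 (B). The products are 0.71 × 0.91 = 0.64 and 0.46 × 0.72 = 0.33.

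**4. Simulation at true SD 0.44, stepping only.** The SD is re-estimated at 10 per group. The trial stops at the new n if that is below 15, and otherwise re-estimates at 15. The final t test is unadjusted. There were 200,000 to 600,000 trials per setting.

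| Rule | Type I error | Type I error if stopped below 15 | Power | Mean n per group |
|---|---|---|---|---|
| A, within-group SD | 0.055 | 0.067 | 0.80 | 12.8 |
| B, within-group SD | 0.058 | 0.083 | 0.87 | 15.2 |
| A, minimum of 15 | 0.051 | n/a | 0.87 | 15.5 |
| B, minimum of 15 | 0.052 | n/a | 0.90 | 16.8 |
| A or B, blinded SD, no minimum | 0.050 | 0.050 | 0.82 to 0.88 | 16.3 to 20.1 |

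Mean n is with a true effect of 0.5. A fixed 15 has exact power 0.852. In trials that stop at exactly 10 per group, Type I error with a within-group SD is about 0.09 to 0.12.

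**5. Other true SDs.** Over 0.30 to 0.65, Type I error with a within-group SD is at most 0.059. Power under the rule, against a fixed 15, is 0.87 to 0.90 against 0.96 at SD 0.36, and 0.79 to 0.86 against 0.67 at SD 0.55.

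**The case against.** The strongest case on the other side is that the re-evaluation does more good than harm. An SD from five subjects per group needs checking. If it is too low, a fixed 15 is underpowered and the rule repairs that, as SD 0.55 shows. A reader might infer that the rule lowers power in general. The figures do not support this: overall power is about 0.79 or higher at every SD tried, close to or above the planned 0.80.

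A reader might also take Type I inflation as established. It is not. It needs a within-group SD, which the article does not specify, and restricting allocation to the trainer is at least compatible with a blinded one. Even then it is under one percentage point overall. The provision that enrolled subjects finish dilutes it further: with an assumed overrun of 2 to 4 per group, Type I error at SD 0.44 is 0.053 to 0.055 and power 0.86 to 0.93.

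Two other stronger readings fail. The look at 15 can only confirm or extend the sample, so it is not a defect in itself. Nor does the article describe an interim significance test or a recalculation from the observed effect. Its effects come from a previous study, and only the variance comes from the trial's own subjects. A recalculation driven by the observed effect would give about 0.07 to 0.08, but that is a different procedure.

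A maximum sample size and operational details may properly sit in a fuller document, so their absence is not held against this article. What stands is that the stated rule permits an end below 15 after the look at 10, with decent probability, and the stated test does not allow for it.

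**Conclusion.** The point holds as a minor one. At SD 0.44 the rule as written has roughly a one-in-three to seven-in-ten chance of ending recruitment below the planned 15, depending on the formula and on whether grasping also counts. With a within-group SD, Type I error is about 0.055 to 0.059 overall and about 0.07 to 0.08 in early-stopped trials at SD 0.44. With a blinded SD it stays at the nominal level. The power cost at SD 0.44 ranges from none (0.87) to five points (0.80 against 0.85 for a fixed 15), and a minimum of 15 lifts power to 0.87 to 0.90. These results rest on the assumptions listed with the calculation, and the early-stopping probabilities on the re-evaluation using the variance alone.

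**What to change.** State that 15 per group is a minimum and that re-evaluation can only raise it. State also that it uses only the variance, with the effects fixed at 0.5 steps and 50 ms, and preferably the blinded one-sample SD. Both looks can stay.

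The cost is a change of wording and the loss of the option to stop at 10 to 14 per group, which lies within the 30 subjects already planned. The blinded SD has a price of its own. If the effect is real, at 10 per group it adds about 10 × 0.5²/(2 × 19) = 0.066 to the variance, so the SD reads about 0.51 instead of 0.44. With the minimum of 15, mean n is then 17.6 to 20.8 per group instead of 15.5 to 16.8. Because the effect is fixed in advance, this known amount can be subtracted. If the sponsor prefers the within-group SD, the minimum of 15 alone keeps Type I error at 0.049 to 0.056 over the SDs tried (rule B).

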## Discussion

This study is among the first to use perturbation-based training as an intervention to reverse age-related impairments in the ability to recover from sudden loss of balance using rapid stepping or grasping reactions. It differs from the previous studies in this area in a number of significant ways. To date, four studies have used perturbations to train stepping reactions; however, two of these focussed on Parkinson's Disease [35,39]. The other two studies showed potential to improve volitional reaction time in older adults [34,36]; however, they did not assess effects of the training on compensatory stepping. No study to date has investigated the potential to use perturbations to train compensatory grasping reactions.

The perturbation-based training program outlined in this protocol is believed to improve on previously proposed programs because: 1) it targets specific aspects of balance-recovery reactions that are known to be impaired in older adults and associated with increased falling risk; 2) the perturbations challenge balance control in multiple directions; 3) the perturbations are unpredictable and hence prevent adaptations that rely on predictive control; 4) the perturbations are applied in a manner that allows for well-controlled progressions in perturbation magnitude; 5) ongoing cognitive and movement tasks are included to increase the generalisability of training; and 6) the training methodology (use of instructions, feedback, etc) adheres to principles that are known to promote optimal motor learning.

We believe that these features will increase the probability that the program will bring about functionally significant improvements in the control of compensatory stepping and grasping. Ultimately, such improvements should help to reduce the incidence of falls. We plan to collect preliminary falls data by monitoring falling in our subjects for a one-year period following the completion of training (using monthly report cards and telephone follow-up [41]); however, investigation of effects on falling is beyond the intended scope of this initial study, and the current sample will likely be too small to determine significant changes in fall rate.

An important factor that may strongly influence the longer-term benefits of the training is the inclusion of some form of maintenance program, which will likely be needed to prevent reversal of the training benefits [82]. Such a maintenance program could potentially involve exercises that can be performed at home, without supervision; however, the development and testing of such a program is beyond the scope of this initial study.

The results of this study, and the initial results from the falls follow-up, will provide new evidence regarding the effectiveness of perturbation-based balance training programs, which may in turn justify additional studies to examine the generalisability of the training benefits to a wider range of balance perturbations and balance-loss situations, as well as larger-scale studies to examine the effects of the training on risk of falling and fall-related injury. If the results are promising, then future efforts will be directed at developing and testing simpler and less expensive methods for administering the perturbations during training, as well as cost-effective exercise programs for long-term maintenance of the training benefits. We anticipate that these efforts will help to guide the development of more effective falls prevention programs, which may ultimately lead to reduced health-care costs and enhanced mobility, independence and quality of life.
